### 2.4. Description of the Clinical Evaluation

#### 2.4.1. Primary outcome: hand dexterity

The Nine-Hole Peg Test (9-HPT) will be administered by the evaluating physician to assess hand dexterity [5,62,63]. Briefly, patients will be trained to perform the test for five consecutive trials. The inter-trial interval will be 1 min. For each trial, the subject begins with the hand resting beside the pegboard. The experimenter initiates the trials with a verbal ready–steady–go command, and times the trial with a digital stopwatch. After training trials, another five trials will be done, recorded, and their sum will be calculated.

The dependent variable is the number of pegs per second computed based on nine pegs placed compared to the time needed to finish the test [63]. In case of inability to complete the test, the variable corresponds to the number of pegs placed divided by the time limit of the test (300 s).

#### 2.4.2. Secondary outcomes

Fatigue will be assessed using the 21-item Modified Fatigue Impact Scale (MFIS), which is relatively short, robust, and reliable [64]. It contains three subscales: cognitive (10 items), physical (9 items), and psychosocial fatigue (2 items). The items are scored from 0 to 4 (0 = Never, 1 = Rarely, 2 = Sometimes, 3 = Often, 4 = Almost always), and respondents are asked to consider their experiences with fatigue during the past four weeks.

Pain will be evaluated using a 0-10 visual analog scale (VAS) for pain. Anxiety and depressive symptoms will be assessed using the Hospital Anxiety and Depression Scale (HADS) [65]. Spasticity, motor power, and cerebellar function will be evaluated using the MAS [44], MRC [43], and ataxia scale scores [45], respectively. The MAS grading will be performed for the three upper limb segments (shoulder adductor, elbow flexor, wrist flexor), obtaining scores that can range from 0 (no increase in muscle tone) to 4 (affected parts rigid in flexion or extension) [44]. The Clinical Global Impression (CGI) and the Comfort Rating Questionnaire (CRQ) will be used to assess patients’ clinical impression and potential side effects [35]. The CRQ evaluates possible side effects (pain perception, tingling, burning, fatigue, nervousness, disturbed concentration, disturbed visual perception, and headache) observed before, during, and 24 hours after stimulation on a 10-point Likert scale. In addition, it contains two dichotomous questions that assess sleep disturbance and phosphene perception during/after stimulation. At the end of the last session of each stimulation block, patients will be asked to guess the type of stimulation to assess for effective blinding (active/sham).

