## Abstract

Background: Cerebellar and motor tracts are frequently impaired in multiple sclerosis (MS). Altered hand dexterity constitutes a challenge in clinical practice, since medical treatment shows very limited benefits in this domain. Cerebellar control is made via several cerebellocortical pathways, of which the most studied one links the cerebellum to the contralateral motor cortex via the contralateral ventro-intermediate nucleus of the thalamus influencing the corticospinal outputs. Modulating the activity of the cerebellum or of the motor cortex could be of help. Method: The main interest here is to evaluate the efficacy of transcranial direct current stimulation (tDCS), a noninvasive brain stimulation technique, in treating altered dexterity in MS. Forty-eight patients will be recruited in a randomized, double-blind, sham-controlled, and crossover study. They will randomly undergo one of the three interventions: anodal tDCS over the primary motor area, cathodal tDCS over the cerebellum, or sham. Each block consists of five consecutive daily sessions with direct current (2 mA), lasting 20 min each. The primary outcome will be the improvement in manual dexterity according to the change in the time required to complete the nine-hole pegboard task. Secondary outcomes will include fatigue, pain, spasticity, and mood. Patients’ safety and satisfaction will be rated. Discussion: Due to its cost-effective, safe, and easy-to-use profile, motor or cerebellar tDCS may constitute a potential tool that might improve dexterity in MS patients and therefore ameliorate their quality of life.

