### 2.5. Experimental Protocol

The first visit is an inclusion visit, where the examining physician will perform the neurologic exam, and verify the inclusion and exclusion criteria. Patients will obtain information regarding the protocol, consent form, and the other questionnaires to be filled. They will be called in the following days to check if he/she agrees to participate in the study and therefore to plan the stimulation sessions. In case of acceptance, an appointment will be scheduled in order to sign the consent form and deliver a booklet containing the VAS for pain to be filled for one week prior to the stimulation week and during the week of stimulation. If present, medications and physical therapy will be kept the same as the previous month. Patients will be asked to restrict stimulant consumptions (e.g., caffeine, nicotine) at least three hours prior to their appointments.

Each patient will be randomly assigned to receive 3 blocks separated by a washout interval of three weeks (anodal tDCS over M1 contralateral to the most affected hand, cathodal tDCS over the cerebellum, and sham over either cortical site). Each block will consist of five 20-min stimulation sessions, applied on day 1 to day 5 (D1 to D5). On D1, dexterity will be quantified based on the time required to perform the 9-HPT. Each patient will be evaluated for fatigue (MFIS), anxiety and depression (HADS), spasticity (MAS), motor power (MRC), and cerebellar function (ataxia scale). Afterwards, tDCS will be performed in a quiet and well-illuminated room with the patient sitting in an armchair without any concurrent cognitive or motor task. The stimulation session will be repeated from D1 to D5. At the end of D5 session, each patient will undergo the same evaluation as done on D1 (9-HPT, MFIS, HADS, MAS, MRC, ataxia scale), as well as the CRQ, CGI, and will be delivered a VAS booklet (pain) to be filled for one week following D5 and for one week prior to the next tDCS block. 

Each patient will be included in the study for 3 months. 2 patients per week will undergo the stimulation block. The study will take place for a total duration of 12 months, and the final data analysis will be performed in less than a year. The schematic diagram of the protocol is illustrated in Figure 3. 

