### 2.6. Patient Withdrawal, Risks and Benefits

No available conditions in the study protocol can be expected to trigger patient’s withdrawal. However, any patient can withdraw consent at any point during the study without any consequences. The side effects related to tDCS are minimal to none. Mild skin irritation has been rarely reported and can be avoided by dipping the stimulating electrodes in a saline solution before installation. Protocols of tDCS have been the subject of many studies with no serious side effects described to date. A well-experienced team will be in charge of performing tDCS. This study is designed to improve knowledge regarding tDCS in MS patients with altered dexterity and cannot provide direct or lasting medical benefit, but the obtained results might serve in guiding the therapeutic use of tDCS in this domain.

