### 2.8. Safety and Adverse Event Reporting

Safety measures have been well proven by Nitsche et al. In fact, the authors demonstrated that tDCS does not cause heating effects under the electrodes and does not elevate the serum neuron-specific enolase level [30,31,33], a sensitive marker of neuronal damage [66]. It does not result in changes of diffusion-weighted or contrast-enhanced MRI, or of pathological electroencephalographic patterns [33]. These protocols were tested in more than 3000 subjects worldwide with no serious adverse events (SAEs), except for some adverse events (AEs) consisting of slight itching under the electrode, mild redness attributed to neutrally driven vasodilation and seldom-occurring headache, fatigue, and/or nausea [32,35]. tDCS was studied in the context of MS, and its efficacy and safety were reported in the context of neuropathic pain [67,68], tactile sensory deficit [69], and fatigue [40,51,70,71,72,73,74,75], to cite a few. Based on the above, we believe that this study design (5 consecutive daily sessions, 20 min per session, and current intensity of 2 mA, with the proposed circuit setup) is safe and harmless.

The investigators are in charge of recording and reporting all the SAEs that might happen throughout the entire research protocol from the time of obtaining consent and throughout the whole period required to monitor the participants. SAEs will be recorded on a comprehensive form provided for this purpose. This form will be completed, printed, dated, signed, and the principal investigator will be promptly notified. Moreover, regardless of the time of onset following the protocol, all the SAEs suspected to be the result of the research protocol should be reported to the investigator when no other reasonable explanation exists. All the other AEs will be reported only on the medical card of each patient and will include the date of onset, characteristics, intensity, duration, etiologies, taken actions, treatments, and resolutions, if any. There are no specific safety measures related to this research and no important safety data to be collected.

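### The CRQ, the only structured side-effect measure taken in every block, does not ask about itching, skin redness or nausea, so comparing these between conditions may rest on incomplete recording

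*Protocol article*

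**What the plan says.** The abstract promises that patients' "safety and satisfaction will be rated". Section 2.4.2 assigns side effects to the Comfort Rating Questionnaire (CRQ): "The CRQ evaluates possible side effects (pain perception, tingling, burning, fatigue, nervousness, disturbed concentration, disturbed visual perception, and headache". These eight items are rated on a 10-point scale, and the form adds "two dichotomous questions that assess sleep disturbance and phosphene perception during/after stimulation". Section 2.5 places the CRQ at the end of the fifth session of each block: after the D1 battery is repeated, the patient completes further measures, "as well as the CRQ, CGI, and will be delivered a VAS booklet (pain". It is therefore completed once per condition.

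The known effects of tDCS are described elsewhere. Section 2.8 reports past experience of "slight itching under the electrode, mild redness attributed to neutrally driven vasodilation and seldom-occurring headache, fatigue, and/or nausea". Section 2.6 adds: "Mild skin irritation has been rarely reported".

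Section 2.8 also gives a second recording route for non-serious events: "All the other AEs will be reported only on the medical card of each patient and will include the date of onset, characteristics, intensity", followed by duration, cause, action taken and resolution. The same section ends: "There are no specific safety measures related to this research and no important safety data to be collected".

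**The concern.** The article names the effects to be expected and, separately, the items that will be asked, and the two lists overlap only in part. The effects left out include those at the electrode site, which are the only side effects that section 2.6 mentions at all.

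At stake is the between-condition comparison of tolerability. Each patient receives both active conditions and sham, so an item asked in every block gives a within-patient comparison at almost no cost. An item that is not asked cannot be recovered by any later analysis, so an analysis plan that is not shown could not close this gap. Skin effects are also plausible cues to whether a block was active or sham, and they would help to interpret the patients' guesses. That last point is a reasonable supposition; the article does not state it.

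**Working it through.** The plan gives no figure to reproduce. The check is an item-by-item comparison.

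| Effect named in section 2.8 | Asked in the CRQ (section 2.4.2)? | Nearest CRQ item |
|---|---|---|
| Itching under the electrode | No | Tingling, burning |
| Redness | No | None |
| Headache | Yes | Headache |
| Fatigue | Yes | Fatigue |
| Nausea | No | None |

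Result: 2 of 5 asked, 3 of 5 not asked. If the skin irritation of section 2.6 is counted as a sixth, separate effect, 4 of 6 are not asked. Tingling and burning are neighbouring sensations but are not itching, and redness is a visible sign that no sensory item captures.

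**Other instruments at the end of a block (section 2.5).** The 9-HPT measures dexterity, the MFIS fatigue, the HADS anxiety and depression, the MAS spasticity, the MRC scale power, the ataxia scale cerebellar function, the CGI clinical impression and the VAS pain. None asks about skin effects or nausea.

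**The medical card (section 2.8).** It records onset date and intensity. Blocks last five days and are separated by three weeks, so an onset date can usually be matched to a condition. The article does not describe a prompt for particular effects or a common scale for intensity.

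**What an asked item would give.** Up to 48 × 3 = 144 patient-blocks would be rated. If no patient reported an effect under one condition, the one-sided 95% upper bound on its rate would be 1 − 0.05^(1/n):

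- n = 48 (all patients, section 2.3): 1 − 0.05^(1/48) = 6.1%
- n = 36 (48 × 0.75, at the 25% dropout allowed in section 2.3): 1 − 0.05^(1/36) = 8.0%
- n = 24 (one sham site, assuming the 48 are split evenly between the two sham setups): 1 − 0.05^(1/24) = 11.7%

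These bounds illustrate the precision available. They do not measure harm. An absence of card entries supports no comparable bound unless it is known that every patient was asked.

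**The case against.** The strongest objection is that the protocol does have a route for these effects. A reader might infer from the mismatch that itching, redness and nausea will simply be missed. The documents do not support that, because section 2.8 sends every other adverse event to a dated card. Nor do they say that card entries depend on patients volunteering them. How such events are elicited is detail that a condensed article may leave to the full protocol or the case report form. Redness can also be seen by the staff who place the electrodes. This objection stands, and it limits the point to the lack of a described systematic question and a common rating.

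A reader might also infer that the trial cannot check whether sham feels like active stimulation. That goes too far. The CRQ rates pain, tingling and burning and asks about phosphenes, and section 2.4.2 has patients guess active or sham at the end of each block. The check is partial but not absent.

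Three further objections carry some weight. Section 2.4.2 summarises a cited questionnaire and does not say that its list is exhaustive. Section 2.8 gives its list as background from earlier studies and does not offer it as a monitoring list for this trial, so the two sections do not contradict each other. The effects are described as slight, mild or rare, and using a published questionnaire unchanged is defensible.

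None of this removes the core: as described, the one structured per-condition measure does not ask about three effects that the protocol itself expects. The closing sentence of section 2.8 on safety data gives no reassurance that they are gathered systematically elsewhere.

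**Conclusion.** The point holds as a minor one. Three of the five adverse events named in section 2.8 are not elicited by the only structured side-effect measure completed in every block, and the article describes no systematic elicitation or common scale for them on the medical card. Comparing them between motor, cerebellar and sham stimulation may therefore rest on incomplete recording. How incomplete cannot be estimated from the document, and the 3 of 5 is a share of list entries, not of events or of risk.

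The conclusion assumes that section 2.4.2 gives the CRQ's items in full and that the unseen forms contain no prompt for these effects. If either assumption is wrong, the point shrinks or disappears. The primary outcome, sample size and randomisation are not affected.

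**What to change.** Add three supplementary items to the CRQ form in every block, on the same 10-point scale and at the same reference times as the existing rated items: itching under the electrodes, skin redness or irritation at the electrode sites, and nausea. Tabulate them by condition and by electrode site, keeping sham over the motor cortex and sham over the cerebellum apart, and report the original CRQ items separately so that they stay comparable with other uses of the questionnaire. Site-specific sham figures will be less precise because they rest on only part of the sample.

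The cost is three extra lines per block and a small amendment to the form. The downside is a slightly longer questionnaire that departs from the published version. A separate skin inspection by staff would be an additional procedure and is not needed for this change. If the full protocol or case report form already prompts for these effects in every block, it is enough to say so and to state how they will be tabulated.

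### The CRQ is meant to rate side effects 24 hours after stimulation but is completed at the end of the D5 session, so it cannot cover the 24 hours after the fifth session or the completed course

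*Protocol article*

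**What the plan says.** Section 2.4.2 of the protocol article describes the CRQ as the instrument for potential side effects. Eight symptoms (pain perception, tingling, burning, fatigue, nervousness, disturbed concentration, disturbed visual perception and headache) are rated as "observed before, during, and 24 hours after stimulation on a 10-point Likert scale". The form also has "two dichotomous questions that assess sleep disturbance and phosphene perception during/after stimulation".

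Section 2.5 sets the schedule. A block is five daily 20-minute sessions, D1 to D5, and each patient receives "3 blocks separated by a washout interval of three weeks". On the last day of a block, "At the end of D5 session, each patient will undergo the same evaluation as done on D1", "as well as the CRQ, CGI, and will be delivered a VAS booklet (pain) to be filled for one week following D5". The text names no later CRQ, next-day call or take-home CRQ page.

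Section 2.8 adds a separate safety route. Serious adverse events are recorded "from the time of obtaining consent and throughout the whole period required to monitor the participants". For the rest, "All the other AEs will be reported only on the medical card of each patient", with date of onset, intensity and duration among the details noted.

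**The concern.** The article states both the window that the CRQ covers and the time at which it is completed, and the two do not fit for the session that has just ended. A patient filling in the form straight after the fifth stimulation has not yet lived through the following 24 hours or the following night. The 24-hour column can be left blank, guessed, or filled from memory of earlier sessions, and nothing in the text fixes which.

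At stake is the structured tolerability record of the exposure under test, which is five consecutive sessions. Section 2.8 itself lists headache and fatigue among the known effects of tDCS, and both are CRQ items. A 24-hour rating after the completed course is what one would want for them, and it cannot be reconstructed later. There is also a risk that one form mixes sessions: the before and during columns may describe D5 while the 24-hour column describes an earlier day.

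**Working it through.** The plan gives no figure on this point, so there is nothing to reproduce. The check compares the CRQ window with its administration time.

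**Inputs**
- CRQ window: up to 24 hours after stimulation (section 2.4.2).
- CRQ administration: once per block, at the end of the D5 session (section 2.5).
- Sessions per block: 5, on consecutive days. Blocks per patient: 3 (section 2.5).
- Patients: 48 (section 2.3).
- Assumption: sessions take place at about the same hour each day.

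**Step 1: which sessions have a complete 24-hour window when the form is filled in?** A session on day *k* qualifies only if *k* + 1 ≤ 5.
- D1 to D4: 2, 3, 4 and 5 are all ≤ 5, so the window is complete for 4 of 5 sessions.
- D5: 6 > 5, so the window is not complete. About 0 of its 24 hours have elapsed.

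**Step 2: how many sessions are affected?**
- CRQ administrations: 48 × 3 = 144.
- Sessions: 48 × 3 × 5 = 720.
- Sessions whose 24-hour window the CRQ cannot cover: 144 × 1 = 144.
- Share: 144 / 720 = 20%. The share is 1/5 for any number of completed blocks, so dropout changes the counts but not the percentage.

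**Step 3: what else covers the period after D5?**
- Pain: the VAS booklet, for one week after D5. Pain perception is one of the eight CRQ symptoms.
- The other seven symptoms, and the part of the sleep and phosphene questions that concerns the time after stimulation: only adverse event recording under section 2.8, which describes no solicited 24-hour rating.
- The next block follows a three-week washout, so its D1 visit is about 21 days later. No visit is described after block 3.

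**Step 4: can D1 to D4 stand in for D5?** Only in part. Their windows have closed by the end of D5 and can be recalled, but they follow one to four sessions, not the completed course.

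**The case against.** Four points can be made on the other side.

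1. *The text says after stimulation, not after D5.* A form given once per block can be read as a summary of the week, with the 24-hour and sleep items answered for sessions already lived through. By the end of D5 that is four of five sessions and four nights. This stands as a possible reading, and it is why a reader should not infer that every one of the 144 forms lacks any usable 24-hour information. It does not remove the problem: the text does not state this reading, and under it the completed course still has no 24-hour CRQ rating.

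2. *The period after D5 is not unobserved.* A reader might infer that after-effects of the course are never seen. The documents do not support that, since the pain VAS runs for a week and adverse event recording continues. Neither replaces a solicited, scored rating of the other symptoms.

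3. *The timing is the same in all three conditions, and each patient is his or her own control.* A reader might infer that delayed effects would be understated, or that the comparison of active with sham would be biased. Neither is shown: the article gives no evidence that effects after the fifth session exceed those after earlier ones, and the gap does not by itself favour either side.

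4. *This is a condensed article, and the schedule figure is not shown.* A take-home part of the CRQ could exist in the full protocol. That cannot be excluded. But the article does give both the window and the administration time, and it does say what goes home after D5: the pain booklet. The legend of Figure 3 has a timing note for the VAS and none for the CRQ. The mismatch lies in what is stated, not in what is left out.

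**Conclusion.** The concern holds in a limited form. As written, the CRQ cannot capture the 24-hour after-effects, sleep included, of the fifth session or of the completed five-session course. That is 144 of 720 sessions (20%), always the last of the block, assuming that all 48 patients complete three blocks and that no later CRQ collection exists outside this article. The 24-hour items can reflect only recall of D1 to D4, and the reference session is not stated.

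Delayed effects could be missed, but the documents do not show that they would be, or that the active and sham conditions would be affected differently. The primary outcome, sample size, randomization and blinding are untouched; the issue is confined to secondary tolerability data. It is worth correcting because the correction is cheap and the data cannot be recovered afterwards.

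**What to change.** Split the CRQ by time of completion. Patients rate the before and during items at the D5 session. They complete the 24-hours-after and sleep items at home, 24 hours after that session, on a page added to the VAS booklet already handed out at D5. State in sections 2.4.2 and 2.5 that the 24-hour rating refers to the D5 session, so that all columns of the form describe the same stimulation.

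The cost is one page in an existing booklet and a wording change in two sections, with no extra visit. The downside is that some pages will not come back. After block 3, where no further visit is described, the page has to be returned together with the VAS booklet.
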